**Fig. 6 Fig6:**
[figure not shown]
Visualisation of three consecutive repetitions of hip abduction with the prescribed TUT

### Statistical analysis

All statistical analyses will be performed according to a pre-established analysis plan. IBM SPSS Statistics ver. 23 will be used as statistical software. The primary analysis will test the between-group difference of the mean deviation from the prescribed TUT per repetition using an unpaired *t*-test. Secondary analyses will test total repetitions, total pulling force per exercise, isometric strength and Kujala Patellofemoral Scale using an unpaired *t*-test. The relative risk (RR) will be calculated for the dichotomized global rating of change to determine the probability of being improved and a Z-test will test the proportion of repetitions that are performed with the prescribed TUT compared with the proportion of repetitions that deviate from the prescribed TUT. Explorative analyses using Pearson’s correlation coefficient will be performed to test: (a) the association between pain and compliance to a specific exercise, and (b) the association between total exercise dose and isometric strength progression.

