Secondary outcomes:The total number of repetitions performed during the intervention period.Pulling force exerted per repetition measured in kilos. This will be expressed as the maximum pulling force during each repetition and corresponds to the resistance used when calculating training volume [26].Isometric strength (presented as Nm/kg) of knee extension, hip extension and hip abduction. Isometric strength will be collected at baseline and follow-up and will be used to explore the association between total exercise dose and changes in isometric strength. Isometric strength will be recorded at baseline and post intervention using a dynamometer (Commander PowerTrack, JTECH Medical, Midvale, Utah, USA) and will follow the protocol by Rathleff et al. [27] for knee extension (ICC= > 0.92). The test for hip abduction and hip extension will follow the test positions of the side-lying hip abduction (ICC = 0.76) and the hip extension with a short lever (ICC = 0.81) described by Thorborg et al. [28].Pain measured on a 100 mm VAS, where 0 mm is no pain and 100 mm is worst pain imaginable. The participants will enter their rating of pain intensity into the BandCizer™-app before and after each exercise. Pain is chosen as an outcome measure to investigate if the participants are more likely to comply to exercises that cause less pain.Kujala Patellofemoral Scale-score (0-100 score, with 0 as complete disability and 100 as fully functional). The Kujala Patellofemoral Scale is a frequently used validated outcome measure in PFP [19, 29, 30] however, it does not come in a Danish version. Therefore a Danish translation has been made with the same content and wordings as the original English version and a backwards translation to English was made according to principles of the translation of patient-reported outcome measures [31], however the translation has not been published. Kujala will be collected at baseline and at follow-up.Global rating of change at follow-up. This will be used to measure the participants’ self-reported recovery on a 7-point Likert scale ranging from “much improved” to “much worse”. Participants are categorised as improved if they rate themselves as “much improved” or “improved” (category 6-7) and categorised as not improved if they rate themselves from “slightly improved” to “much worse” (category 1-5). A 7-point Likert scale to assess self-reported change from baseline has previously been used in studies resembling this study [7, 19].

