### Sample size and power considerations

It is expected that the feedback group will have a TUT close to the recommended 8 s per repetition whilst the control group will have a TUT of 6.5 s which is close to the results of an unpublished study (Rathleff et al. *in review*). Based on a standard deviation of 1.22, which was found in the before-mentioned study, and a two-sided 5 % significance level and a power of 80 %, a sample size of 15 participants per group will be necessary. Taking into consideration possible drop-outs, we will include a total of 40 participants.

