### Randomisation

Forty adolescents diagnosed with PFP will be block randomized in block sizes of 2 to 8 (1:1) into 2 parallel groups of 20 participants using a random number generator on www.random.org. A researcher not involved in the study will generate the allocation sequence and is the only person who will know the block sizes. In practice, after all baseline measurements have been made, the primary investigator will take a sequentially numbered opaque sealed envelope in which allocation to either the feedback group or the control group has been previously determined.

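### Isometric strength and Kujala have baseline values, but the stated unpaired t-test does not adjust for them and does not say whether follow-up or change is tested

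*Protocol article*

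**What the plan says.** The secondary outcomes list under Outcomes provides two measurements for each of these endpoints. For strength (knee extension, hip extension and hip abduction, in Nm/kg): "Isometric strength will be collected at baseline and follow-up". For function: "Kujala will be collected at baseline and at follow-up".

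The Statistical analysis section names the between-group test: "Secondary analyses will test total repetitions, total pulling force per exercise, isometric strength and Kujala Patellofemoral Scale using an unpaired" *t*-test. No covariate is mentioned, and the tested quantity (value at follow-up or change from baseline) is not defined. In that section, change in strength appears only in an exploratory correlation, "the association between total exercise dose and isometric strength progression".

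Under Randomisation, participants are "block randomized in block sizes of 2 to 8 (1:1) into 2 parallel groups of 20 participants". No stratification by baseline strength or Kujala is described. The section also refers to a separate plan that is not at hand: "All statistical analyses will be performed according to a pre-established analysis plan".

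**The concern.** Three strength measures and Kujala each have a baseline value that probably predicts the follow-up value to some degree. Neither the allocation scheme nor the stated test makes use of that relation. With at most 20 per arm, the arms can differ at baseline by chance, and part of that difference then sits in the estimated effect.

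The wording also permits two different analyses. A comparison of follow-up values carries a baseline imbalance forward in its own direction. A comparison of change scores carries it in the opposite direction. The article's text does not settle which is meant, so the same data could give noticeably different answers under the one named test.

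At stake are the precision and interpretability of four secondary comparisons. The sample size section covers only time under tension, so these comparisons have no power calculation of their own.

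**Working it through.** **Plan's own figure.** There is none on this point. The article gives no sample size, power or detectable effect for strength or Kujala, and its one sample size calculation is for a different outcome.

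**Inputs.**
- n = 20 per arm (Randomisation).
- Baseline and follow-up values for each measure (Outcomes).
- Correlation r between baseline and follow-up: not given, so assumed from 0.3 to 0.8.
- Also assumed: equal SDs at the two visits, and a linear relation with a common slope. All effects are in units of that SD.

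**Step 1: chance imbalance.** The baseline mean difference d has standard deviation √(2/n) = √(2/20) = 0.316 SD. From the normal distribution, P(|d| > 0.3 SD) = 34% and P(|d| > 0.5 SD) = 11%. If only 15 per arm were analysed, the standard deviation would be √(2/15) = 0.365 SD.

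**Step 2: shift from a one-standard-error imbalance.** Given d, the follow-up comparison shifts by r·d and the change comparison by (r − 1)·d. ANCOVA removes this shift in expectation under the linear relation.

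**Step 3: variance of the group difference, relative to a t-test on follow-up values.** Follow-up: 1. Change: 2(1 − r). ANCOVA: 1 − r². ANCOVA relative to change is therefore (1 − r²) / [2(1 − r)] = (1 + r)/2.

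| r (assumed) | Shift, follow-up (SD) | Shift, change (SD) | ANCOVA vs follow-up | Variance cut | ANCOVA vs change | Variance cut |
|---|---|---|---|---|---|---|
| 0.3 | +0.09 | −0.22 | 0.91 | 9% | 0.65 | 35% |
| 0.5 | +0.16 | −0.16 | 0.75 | 25% | 0.75 | 25% |
| 0.6 | +0.19 | −0.13 | 0.64 | 36% | 0.80 | 20% |
| 0.7 | +0.22 | −0.09 | 0.51 | 49% | 0.85 | 15% |
| 0.8 | +0.25 | −0.06 | 0.36 | 64% | 0.90 | 10% |

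**Step 4: effect detectable with 80% power.** Noncentral t, 20 per arm, two-sided 5%, with ANCOVA's lost degree of freedom ignored.

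| r (assumed) | Follow-up t-test (SD) | Change t-test (SD) | ANCOVA (SD) |
|---|---|---|---|
| 0.3 | 0.91 | 1.08 | 0.87 |
| 0.5 | 0.91 | 0.91 | 0.79 |
| 0.6 | 0.91 | 0.81 | 0.73 |
| 0.7 | 0.91 | 0.70 | 0.65 |
| 0.8 | 0.91 | 0.58 | 0.55 |

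**Step 5: what ANCOVA costs.** With 40 participants the residual degrees of freedom fall from 38 to 37. The factors in Step 3 treat the slope as known. For a normally distributed baseline, estimating it multiplies the ANCOVA variance by about 1 + 1/(40 − 4) = 1.03. This trims the smallest gains: at r = 0.3, 0.91 × 1.03 = 0.94 against follow-up, and at r = 0.8, 0.90 × 1.03 = 0.93 against change. It does not alter the pattern.

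**The case against.** The strongest defence is that the unpaired t-test is a valid analysis of a randomised trial. It is unbiased over randomisations and keeps its type I error, and its standard error already allows for chance imbalance. Regression to the mean affects both arms equally in expectation. All of this stands. The cost is precision, plus an avoidable shift once a particular imbalance has occurred.

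A second defence is that the baseline may well be used. A reader might infer that the plan throws the baseline away, but the article does not say so. It speaks of change in strength in connection with the dose correlation, and a t-test on change would use the baseline, though without adjusting for it. This also stands. The large gains apply only if follow-up values are tested. If change is tested and r is high, ANCOVA gains little (10% at r = 0.8).

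Third, these outcomes are secondary, and the main aim concerns time under tension. This stands and limits the weight of the point.

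Fourth, the unseen analysis plan may define the endpoint or add a covariate. This stands only in part. The article does not leave the method open: it names a test, and that test takes no covariate. If the plan specifies ANCOVA, the article's wording needs correcting to match.

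Two further inferences lack support. One is that baseline noise dominates these comparisons. Even at r = 0.7 the baseline would explain 49% of the follow-up variance, and r itself is unknown. The other is that strength varies more between adolescents than it changes in six weeks. The article gives neither a between-person SD nor an expected change.

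**Conclusion.** The point holds as one of efficiency and definition. For three strength measures and Kujala, the stated test makes no baseline adjustment and leaves the tested quantity undefined. It should not be read as a claim of bias on average or of an inflated error rate.

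For r between 0.3 and 0.8, the variance that ANCOVA would save is 9% to 64% if follow-up values are tested, and 35% down to 10% if change is tested. ANCOVA has the smaller variance under both readings across this range. A typical (one-standard-error) imbalance of 0.32 SD would move a follow-up comparison by 0.09 to 0.25 SD, and a change comparison by 0.22 to 0.06 SD the other way. These sizes rest on the assumed r, equal SDs at both visits, a linear relation, and 20 analysed per arm.

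The trial's main conclusion is not affected. The article describes no baseline value for the primary outcome or for total repetitions, so the point does not extend to them.

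**What to change.** In the Statistical analysis section, take the isometric strength measures and Kujala out of the list of unpaired t-tests. State instead that each will be analysed by linear regression of the follow-up value on treatment arm and that measure's own baseline value, and that the adjusted mean difference will be reported with its 95% confidence interval. This also settles which quantity is tested, because adjusting for baseline gives the same arm effect whether follow-up or change is the dependent variable. Bring the separate analysis plan into line if it differs.

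The cost is a change of wording and one degree of freedom per model. Both measurements are already scheduled, the named software fits the model, and neither the sample size nor the primary analysis changes.

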### Intervention

Once informed consent has been gained, the participants will be instructed in performing three exercises with an elastic band; knee extension (Fig. 1), hip abduction (Fig. 2) and hip extension (Fig. 3). These types of exercises have previously been tested and found effective in patients with PFP [2, 19, 20]. The exercise descriptors, which are adopted from the mechano-biological descriptors from Toigo and Boutellier [21], are described in the table below (Table 1).

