**Fig. 3 Fig3:**
[figure not shown]
Hip extension. The subject provided consent to appear

**Table 1 Tab1:** Exercise descriptors

	Knee extension (Fig. 1)	Hip abduction (Fig. 2)	Hip extension (Fig. 3)
1. Load magnitude	10-12 RM	10-12 RM	10-12 RM
2. Number of repetitions	10	10	10
3. Number of sets	3	3	3
4. Rest in between sets	1 min 50 seconds	1 min 50 seconds	1 min 50 seconds
5. Number of exercise interventions (per (day) or week)	3/week	3/week	3/week
6. Duration of the experimental period ((day) or weeks)	6 weeks	6 weeks	6 weeks
7. Fractional and temporal distribution of the contraction modes per repetition and duration (s) of one repetition	3 s concentric	3 s concentric	3 s concentric
	2 s isometric	2 s isometric	2 s isometric
	3 s eccentric	3 s eccentric	3 s eccentric
8. Rest in-between repetitions ((s) or (min))	No	No	No
9. TUT ((s) or (min))	8 s/repetition	8 s/repetition	8 s/repetition
	80s/set	80s/set	80s/set
	4320 s/total intervention	4320 s/total intervention	4320 s/total intervention
10. Volitional muscular failure	Yes	Yes	Yes
11. Range of motion	90° to 180^o^	0° to 45^o^	45° hip flexion to 0° hip flexion/extension
12. Recovery time in-between exercise sessions ((h) or (d))	48 h	48 h	48 h
13. Anatomical definition of the exercise (exercise form)	Knee extension is performed with the participant sitting in 90^0^ knee flexion. The elastic band is looped around the ankle and around a solid anchor near the floor under the participant (Fig. 1). The knee is extended to approximately 180^0^.	Hip abduction will be performed in standing with the elastic band looped around the ankle and anchored to the wall at ankle height. The stance leg will be in front of the band and the target hip in a slight internal rotation (Fig. 2). Hip abduction will then be performed to approximately 45^0^.	Hip extension will be performed in standing with target hip in 45^0^ hip flexion. One end of the elastic band fixated at knee height and looped around the back of the knee (Fig. 3). The hip is then extended to approximately 0° hip extension whilst maintaining a neutral lumbo-pelvic position.

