Participants will receive an elastic band, a BandCizer™ and an iPad with the BandCizer™-app. Before and after each exercise they are instructed to record their knee pain on a 100 mm VAS that is integrated in the app. They are instructed to perform the exercises three times each week during the 6-week intervention. Twice a week the exercises are performed at home whilst the last exercise session will be a group training session supervised by a physiotherapist. In connection with the initial instruction of the exercises, 10-12 RM will be determined by shortening the elastic band to a length where the participants feel that they will not be able to perform more than 10 repetitions. The pulling force exerted when the exercise is performed correctly will be measured by the BandCizer™ and recorded by the investigator. If the participants become able to perform more than 10 repetitions during the intervention period, they will be instructed to shorten the band or change to a different grade of band. In this situation a new measurement of recommended pulling force will be made.

The feedback group will have access to live visual and auditory feedback on TUT and pulling force from the BandCizer™-app when they perform the exercises. Controls will only receive visual feedback on pulling force.

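### The Z-test on repetitions sets a proportion against its own complement; if read as a between-arm test, it appears to ignore clustering within participants (secondary analysis)

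*Protocol article*

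**What the plan says.** The Statistical analysis section first sets the primary analysis, an unpaired t-test between groups on the average departure from the 8 s time under tension (TUT). It then lists secondary tests. One of them reads: "a Z-test will test the proportion of repetitions that are performed with the prescribed TUT compared with the proportion of repetitions that deviate" (the deviation meant is from the 8 s target). The clause names neither the groups nor a summary per participant.

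The number of repetitions follows from Table 1 and the Intervention section. Table 1 gives 10 in the row "2. Number of repetitions" and 3 in the row "3. Number of sets". In the Intervention section, "the participants will be instructed in performing three exercises with an elastic band", and "They are instructed to perform the exercises three times each week during the 6-week intervention". Table 1 also gives a total TUT for each exercise of "4320 s/total intervention". The Randomisation section allocates 40 adolescents "into 2 parallel groups of 20 participants".

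The section on analysis population and missing data counts prescribed repetitions that were not performed as non-compliance. The Statistical analysis section refers to a pre-established analysis plan, which is not shown.

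**The concern.** There are two problems, and they are mostly alternatives.

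- **Read literally**, the test contrasts the on-target share with the off-target share. Neither share belongs to an arm, so the result says nothing about the Hypothesis section's comparison of feedback with control.
- **Read as a between-arm test**, which is probably what was meant, the unit is still the repetition. Repetitions by one adolescent resemble each other, and only 40 people are randomised. An ordinary Z-test on pooled repetitions would give a standard error that is too small and too many false positives.

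This is the only listed test of how many repetitions met the TUT prescription. A share of repetitions done as prescribed is easy to read and likely to be quoted, so a misleading p-value attached to it would matter, although the analysis is secondary.

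**Working it through.** **Inputs.** From the document: 10 repetitions, 3 sets, 3 exercises, 3 sessions a week for 6 weeks (18 sessions), 8 s per repetition, 40 participants allocated 20 to 20. Not in the document: the ICC of on-target status within a participant, assumed here to lie between 0.001 and 0.30.

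**Step 1: reproduce the plan's own figure.** 10 × 3 × 18 = 540 repetitions per exercise, and 540 × 8 s = 4320 s, which agrees with Table 1. Then 540 × 3 exercises = 1,620 repetitions per participant, 1,620 × 20 = 32,400 per arm, and 1,620 × 40 = 64,800 in all.

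**Step 2: the test as worded.** Let p be the share on target. The other share is 1 − p, and p = 1 − p only when p = 0.5. The statistic is z = (p − 0.5) / √(0.25/N).

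- With N = 64,800, √(0.25/N) = 0.00196, so any p further than 1.96 × 0.00196 = 0.0038 from 0.5 is significant. An observed p of 0.49 gives z = −5.09.
- With N = 32,400 (one arm), the limit is 0.0054, and p = 0.49 gives z = −3.60.
- If the complements were entered as two independent samples, the variance used would be 2p(1 − p)/N. The variance of p − (1 − p) = 2p − 1 is 4p(1 − p)/N, so z would be too large by a further √2 = 1.41.

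The value 0.5 has no role in the trial, and none of these results involves the allocation.

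**Step 3: the between-arm reading.** With m = 1,620 repetitions per participant, the design effect is DE = 1 + (m − 1) × ICC = 1 + 1,619 × ICC. The true size of a nominal two-sided 5% test is 2 × [1 − Φ(1.96/√DE)].

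| Assumed ICC | DE | Effective repetitions (64,800/DE) | True size, formula | True size, simulation |
|---|---|---|---|---|
| 0.001 | 2.6 | about 24,700 | 23% | not run |
| 0.01 | 17.2 | about 3,770 | 64% | 64% |
| 0.05 | 82 | 791 | 83% | 83% |
| 0.10 | 163 | 398 | 88% | 88% |
| 0.30 | 487 | 133 | 93% | 93% |

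The simulation used 20,000 beta-binomial trials per ICC, 20 participants per arm, 1,620 repetitions each and a mean share of 0.5 in both arms.

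**Step 4: lower adherence.** If each participant did only 400 repetitions and the ICC were 0.05, DE = 1 + 399 × 0.05 = 20.95, and the size would be about 67%.

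**Step 5: the repair.** In the same simulated data, an unpaired t-test on one proportion per participant rejected a true null in 4.9% to 5.0% of runs for ICC 0.01 to 0.30.

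**The case against.** The strongest reply is that this is a loosely worded sentence in a journal article. The missing-data section says that participants are analysed by allocated group, which supports a between-group intent. The clause gives no sample size and no pooling rule, so independence of repetitions is inferred from the choice of a plain Z-test; the document does not state it. That stands, and it is why the clustering point is put as what the test appears to do. It does not rescue the sentence. As printed, the contrast is between complements, and a Z-test on a proportion of repetitions most naturally takes the repetition as its unit.

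It is also fair to say that the false-positive rates belong only to the between-arm reading, so they do not add to the complement problem. They rest on an assumed ICC and, in the table, on full adherence, which the protocol itself does not expect. A reader might infer that such a test would almost always be significant with no effect. At an ICC of 0.001 the size is 23%, so that does not hold over the whole range, although even 23% is far from 5%.

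A reader might also infer that the proportion is undefined or close to zero, because TUT is continuous and the article gives no tolerance around 8 s. The document does not support that as a finding. A tolerance band is a detail that an article commonly leaves to the analysis plan, and the plan referred to is not shown.

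Finally, the other parts of compliance are covered: total repetitions, pulling force and average TUT departure each have their own t-test.

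**Conclusion.** The point holds for a secondary analysis, and the sentence should be corrected. The complement problem rests on the wording alone and needs no assumption: as written, the test is of p = 0.5 and does not compare the arms. The clustering problem applies if a between-arm test was meant. It rests on the inference that repetitions would be pooled, on an assumed ICC, and on all 1,620 prescribed repetitions being done. Under those assumptions the true size of a nominal 5% test runs from about 23% to about 93%.

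A reader might take this to undermine the trial's conclusion. It does not. The primary analysis is a between-group t-test on a different summary, and neither it nor the sample size depends on this Z-test. The proportion is not among the secondary outcomes listed under Outcomes either.

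**What to change.** Replace the Z-test clause with a between-group comparison that uses one proportion per participant, tested by an unpaired t-test or a permutation test. Logistic GEE with the participant as cluster is an alternative; with only 40 clusters, its robust standard errors need a small-sample correction.

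Two definitions go with it:

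- **Denominator.** It must agree with the missing-data section, where repetitions not performed count as non-compliance. That points to the prescribed number. Using performed repetitions would change the quantity estimated and leave it undefined for a participant with none. The same section imputes means for drop-outs and for participants with no repetitions, so the text should say how those rules apply to this proportion.
- **On-target band.** Take it from the pre-established analysis plan, or fix it before data are seen by arm.

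The cost is a sentence or two of wording and a larger p-value that reflects 40 randomised participants. Data collection, sample size and the primary analysis do not change.
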